**Methods/design:**

The study involves a cluster randomisation trial to be conducted within a Child and Adolescent Mental Health Service in rural Australia. All clinicians in the service will be invited to participate. Participating clinicians will be randomised via block design at each of four sites to (a) training and delivery of IPT, or (b) TAU. The primary measure of impact on care will be a clinically significant change in depressive symptomatology, with secondary outcomes involving treatment satisfaction and changes in other symptomatology. Participating adolescents with significant depressive symptomatology, aged 12 to 18 years, will complete assessment measures at Weeks 0, 12 and 24 of treatment. They will also complete a depression inventory once a month during that period. This study aims to recruit 60 adolescent participants and their parent/guardian/s. A power analysis is not indicated as an intra-class correlation coefficient will be calculated and used to inform sample size calculations for subsequent large-scale trials. Qualitative data regarding process implementation will be collected quarterly from focus groups with participating clinicians over 18 months, plus phone interviews with participating adolescents and parent/guardians at 12 weeks and 24 weeks of treatment. The focus group qualitative data will be analysed using a Fourth Generation Evaluation methodology that includes a constant comparative cyclic analysis method.

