## Methods/Design

### Sample

The research is being conducted within the LRH CAMHS in rural Victoria, Australia. The service provides care for children and adolescents across 40,000 square kilometres with a population of 236,000. All clinicians, employed full- or part-time within the LRH CAMHS, other than the principle investigator, are invited to participate. At the time of writing this includes 18 clinicians based at four sites. The clinicians comprise psychologists, social workers, occupational therapists, mental health nurses and a psychiatry registrar. The trial aims to include a minimum of 60 adolescent clients of LRH CAMHS, aged 12 to 18 years inclusive, to be recruited over 12 months. The sample size was determined on the basis of logistic feasibility and resource constraints. In addition, given the lack of information about the likely size of the intra-class correlation coefficient (ICC), one intention of this study is to estimate this statistic to assist in sample size calculation for a larger subsequent effectiveness trial [20].

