#### Randomisation

A cluster randomisation design was chosen over simple client randomisation to overcome the obstacles of randomizing adolescents to treatment streams (i.e. to specific clinicians). Randomisation of adolescents could not be assured given limitations on the availability of specific clinicians at any given time and site.

The clinical assignment allocation process involves block randomisation of participating clinicians within each of the four sites to either IPT training or TAU. Allocation of clients to clinicians continues as per usual practice of availability. Randomisation was conducted centrally.

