## Analysis of results

### Quantitative analysis

Analysis will adopt an intention-to-treat design. The primary quantitative outcome measure will be change in depressive symptomatology. This will be evaluated as (a) the proportion of clients per treatment group with remission of depressive symptoms, defined as RADS-2 score below the clinical cut-off; (b) the proportion of clients per treatment group with clinical improvement of depressive symptoms, defined as having a 50% or higher reduction of depressive symptoms; (c) the difference in mean depressive symptoms post-treatment. The secondary quantitative outcome measure will be group differences in adolescent and parent/guardian satisfaction with treatment at 12 weeks and 24 weeks after start of treatment. Treatment acceptability will also be measured by proportion of clients per treatment group who do not complete treatment [16].

The quantitative analyses will compare group differences (i.e. remission, clinical improvement, mean difference, and non-completion) between the IPT and TAU groups. These analyses will allow estimation of the effect size of IPT on these outcomes. Comparison will be made between baseline and outcomes at 12 weeks and 24 weeks from start of treatment. Our main aim is one of estimation rather than hypothesis testing. Thus, effect sizes with 95% confidence intervals will be calculated in favour of significance testing in order to provide information for subsequent trials.

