To fit in with the CAMHS realities, a cluster randomisation design was chosen over client randomisation. The consideration of client randomisation raised concerns for both clinicians and researchers. It was not feasible to do client randomisation given the scarcity of clinicians based at each of the four rural sites. At any given time a clinician from the allocated treatment stream may not be available at that site to work with the adolescent. For example, one site may have only one participating clinician and others only one for each treatment stream. Cluster randomisation provided the solution to this dilemma. It has the advantage of allowing usual-care allocation of clients and would provide an estimate of the ICC which would assist sample size planning in a larger-scale subsequent trial, if judged to be feasible and valuable.

Given the uncertainties existing regarding the safety and efficacy of psychopharmacological treatment of adolescents [7], it is important that effective psychological interventions are readily available for the treatment of adolescent depression. IPT appears a useful intervention for this purpose, given that it is described as easily learned and applied by a range of mental health professionals [13,14].

The study of TAU, however, is also an important component of the study. First, there has been little study of what TAU specifically entails in a multidisciplinary rural mental health service. Clarification of the content of this is important if we are to understand or evaluate it or compare it to alternative forms of treatment. Second, the effectiveness of TAU is unknown. If TAU proves as effective in practice as identified evidence-based practices then questions about the value of implementation efforts regarding the latter may be raised. Definitive answers about effectiveness of TAU compared to IPT in practice will, however, require large sample sizes and replication of results with different studies, a challenging endeavor within community practice.

The real-world context of this study means that it faces important limitations. First, key variables cannot be controlled in this environment. The methodology is impacted by such factors as clinician turn-over, mixed attitudes to involvement in research, questions of treatment fidelity, challenges of data collection, amongst others. The decision was made, therefore, to describe the variables rather than attempt to control.

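### The 95% confidence intervals are tied to client-level group comparisons with no allowance for the randomised clinicians or the site blocks; unadjusted, they would be too narrow if the clinician ICC is positive

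*Protocol article*

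**What the plan says.** The Randomisation section describes "block randomisation of participating clinicians within each of the four sites to either IPT training or TAU". Clients are not randomised: "Allocation of clients to clinicians continues as per usual practice of availability". On numbers, the Sample section says "At the time of writing this includes 18 clinicians based at four sites" and "The trial aims to include a minimum of 60 adolescent clients of LRH CAMHS". All clinicians are invited; how many take part is not stated. There is no power calculation: "The sample size was determined on the basis of logistic feasibility and resource constraints".

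The Quantitative analysis section defines the primary outcome through the proportions of clients in each treatment group who remit or improve, and through a difference in mean symptoms. It adds satisfaction and non-completion, and compares the IPT and TAU groups on these. It declares estimation, not hypothesis testing, to be the main aim, so that "effect sizes with 95% confidence intervals will be calculated in favour of significance testing". It names no model, variance method, cluster term or site term.

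The abstract says that "an intra-class correlation coefficient will be calculated and used to inform sample size calculations for subsequent large-scale trials". The Sample section and the Discussion give the ICC the same purpose. The Discussion also says that the cluster design is likely to detect and account for variability between groups. To explain why clients were not randomised, it notes that "one site may have only one participating clinician and others only one for each treatment stream".

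**The concern.** Clients of the same clinician share that clinician's skill, style and case mix, so their outcomes may be correlated. The information about IPT versus TAU then depends on the number of clinicians as well as the number of clients. An interval that treats 60 clients as 60 independent observations leaves out the between-clinician variance and takes its degrees of freedom from clients instead of clusters.

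The authors plainly have clustering in mind, since they plan to estimate the ICC. But each place that gives the ICC a purpose points to the next trial, and none links it to this trial's intervals. The one sentence on handling clustering here assigns the job to the design. Randomising by clinician creates the correlation; it does not allow for it.

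Interval estimation is the declared main aim, so the width of the intervals is a principal quantitative product. If it is understated, the larger trial that this study is meant to inform inherits effect estimates that look more precise than they are.

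**Working it through.** The plan states no ICC, standard deviation, effect size or interval width, so there is no figure of its own to reproduce. The check asks how far a client-level interval would fall short.

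**Inputs from the Protocol article**
- Clients: N = 60, the stated minimum (Sample).
- Clusters: K = 18 clinicians, an upper limit (Sample).
- Confidence level: 95%, taken as two-sided (Quantitative analysis).

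**Assumed inputs**
- Clinician ICC: 0.05, 0.10 and 0.20.
- Equal caseloads, 30 clients per arm.
- As a second case, only 10 clinicians recruiting.

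**Step 1. Clients per clinician.** m = 60/18 = 3.33.

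**Step 2. Design effect.** DE = 1 + (m − 1) × ICC.
- ICC 0.05: 1 + 2.33 × 0.05 = 1.12
- ICC 0.10: 1 + 2.33 × 0.10 = 1.23
- ICC 0.20: 1 + 2.33 × 0.20 = 1.47

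**Step 3. Coverage of an unadjusted interval.** A client-level interval takes its standard error from about 58 degrees of freedom, so the normal approximation serves: coverage = 2Φ(1.96/√DE) − 1.

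**Step 4. Width of an adjusted interval relative to the client-level one.** Ratio = √DE × t(0.975, K − 2)/t(0.975, N − 2). For K = 18 the t ratio is 2.120/2.002 = 1.059. For K = 10 it is 2.306/2.002 = 1.152.

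| Clinicians | ICC | DE | Coverage of nominal 95% CI | Width ratio, √DE alone | Width ratio with t on K − 2 |
|---|---|---|---|---|---|
| 18 | 0.05 | 1.12 | 93.6% | 1.06 | 1.12 |
| 18 | 0.10 | 1.23 | 92.2% | 1.11 | 1.18 |
| 18 | 0.20 | 1.47 | 89.4% | 1.21 | 1.28 |
| 10 | 0.05 | 1.25 | 92.0% | 1.12 | 1.29 |
| 10 | 0.10 | 1.50 | 89.0% | 1.22 | 1.41 |
| 10 | 0.20 | 2.00 | 83.4% | 1.41 | 1.63 |

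Simulated client-level t intervals for a difference in means, with 30 clients per arm, gave 93.5%, 92.3% and 89.1% for 18 clinicians and 91.9%, 89.0% and 82.9% for 10. At ICC 0 they gave 95.0%, as they should.

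**Step 5. Uneven caseloads.** DE = 1 + ((CV² + 1) × m − 1) × ICC, where CV is the coefficient of variation of caseload. With 18 clinicians and an assumed CV of 0.65, DE is 1.19, 1.37 and 1.75. Coverage is 92.8%, 90.5% and 86.2%, and the width ratio with t on 16 degrees of freedom is 1.15, 1.24 and 1.40.

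**Step 6. Scale.** With 30 per arm, the half-width of a standardised mean difference is 1.96 × √(2/30) = 0.51 SD unadjusted. Multiplying by √DE for 18 clinicians gives 0.56 SD at ICC 0.10 and 0.61 SD at ICC 0.20.

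**The case against.** The strongest reply is that no interval method is fixed. Proportions and means of clients are legitimate summaries in a cluster trial when their intervals are cluster-robust or come from a mixed model. The document is a condensed article, and a named model with its small-sample correction is the kind of detail that a fuller protocol or analysis plan may hold. The authors know that the trial is clustered, and no passage says that the ICC has no other use.

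Much of that stands. A reader might infer that the intervals will certainly be too narrow. The document does not support this, because the conclusion needs two conditions: no adjustment, and a positive ICC. Three further inferences also go too far:
- **Site.** Leaving a stratification factor out of the analysis tends to widen intervals, so it cannot be counted as a second source of narrowness, and the net direction is not certain.
- **Single-clinician site.** The Discussion says only that this may occur. Confounding of arm with site there is a possibility to plan for, not a known defect.
- **Lower coverage.** Applying t on 16 degrees of freedom to the client-level interval gives worse figures, but the formula fails its own check: it returns about 93% at ICC 0, where coverage is 95%.

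It is also fair that the sample size rests on feasibility, that no hypothesis test is planned, and that the estimates will be imprecise either way.

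The reply does not remove the point. The plan describes the comparison at client level, states a purpose for the ICC that leaves out this trial's intervals, and attributes the handling of clustering to the design. That last statement is wrong as written, whatever an unseen plan contains.

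**Conclusion.** The point holds in conditional form. The article ties its effect sizes and 95% intervals to client-level comparisons without allowing for the randomised unit or the site blocks, and the Discussion credits the design with what only the analysis can do. Followed as it reads, this gives intervals that are too narrow if the clinician ICC is positive.

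The size is modest if all 18 clinicians recruit evenly: coverage of about 94% to 89%, and adjusted intervals 12% to 28% wider, over assumed ICCs of 0.05 to 0.20. It becomes more serious if caseloads are uneven or clinicians few: with 10 clinicians, coverage is about 92% to 83%. These ranges rest on assumed ICCs, caseload patterns and numbers recruiting, because the document gives none of them. They leave out any offsetting effect of ignoring site.

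**What to change.** In the Quantitative analysis section, state that all between-arm estimates and 95% intervals (remission, improvement, mean symptoms, satisfaction, non-completion) come from one of two approaches: a model with a random effect for the randomised clinician and a small-sample correction, such as Kenward-Roger or t based on the number of clusters; or an analysis of clinician-level summaries.

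Include site as the stratification factor where both arms are represented, and say that small sites will be combined where they are not, so that their clients still contribute. Amend the Discussion sentence to say that the analysis, not the design, accounts for clustering.

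The change is to wording only. Recruitment, data collection and treatment are untouched, and the ICC is to be estimated anyway. The cost is somewhat wider intervals.

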### Qualitative analysis

The qualitative data will be analysed using a Fourth Generation Evaluation methodology [30] that includes a constant comparative cyclic analysis method. This involves initial scanning of the data sets, development of themes from the data sets, comparison of analysed data across the data sets and formulation of final recommendations for the improvements in similar CAMHS research trials.

## Discussion

This protocol is the result of collaboration between a rural CAMHS and Monash University. It developed from an interest within CAMHS of implementing and evaluating a focused evidence-based practice clinic. The key interests of CAMHS and academic collaborators are on the evaluation of practice and recording the process issues associated with implementation of a clinical trial in CAMHS. The study aims to inform development of a larger scale definitive clinical trial.

The challenges of linking research and practice in health services are well documented. With the increased pressure on services to deliver and document evidence-based practice, the issues concerning integration of evidence and practice are increasingly important. This study seeks to look at these process issues arising in a rural CAMHS embarking on a clinical trial.

A key aim of the project trial is to assess the feasibility of conducting effectiveness trials of short-term psychological interventions in a rural CAMHS. To assess issues of feasibility and to aid interpretation of trial results, a combination of qualitative and quantitative methodologies will be applied. The facilitated discussion groups with clinicians, and interviews with adolescent and parent/guardian participants, plus a research diary, aim to capture the process issues as they arise and any related complexities and solutions uncovered during the trial. These findings are considered important to assist further mental health services researchers in the design of similar future ventures. They are also important in a political environment of increasing evidence-based practice pressure. Documentation of the implementation obstacles and facilitators can practically inform discussions, expectations and decisions in this area.

To fit in with the CAMHS realities, a cluster randomisation design was chosen over client randomisation. The consideration of client randomisation raised concerns for both clinicians and researchers. It was not feasible to do client randomisation given the scarcity of clinicians based at each of the four rural sites. At any given time a clinician from the allocated treatment stream may not be available at that site to work with the adolescent. For example, one site may have only one participating clinician and others only one for each treatment stream. Cluster randomisation provided the solution to this dilemma. It has the advantage of allowing usual-care allocation of clients and would provide an estimate of the ICC which would assist sample size planning in a larger-scale subsequent trial, if judged to be feasible and valuable.

Given the uncertainties existing regarding the safety and efficacy of psychopharmacological treatment of adolescents [7], it is important that effective psychological interventions are readily available for the treatment of adolescent depression. IPT appears a useful intervention for this purpose, given that it is described as easily learned and applied by a range of mental health professionals [13,14].

The study of TAU, however, is also an important component of the study. First, there has been little study of what TAU specifically entails in a multidisciplinary rural mental health service. Clarification of the content of this is important if we are to understand or evaluate it or compare it to alternative forms of treatment. Second, the effectiveness of TAU is unknown. If TAU proves as effective in practice as identified evidence-based practices then questions about the value of implementation efforts regarding the latter may be raised. Definitive answers about effectiveness of TAU compared to IPT in practice will, however, require large sample sizes and replication of results with different studies, a challenging endeavor within community practice.

The real-world context of this study means that it faces important limitations. First, key variables cannot be controlled in this environment. The methodology is impacted by such factors as clinician turn-over, mixed attitudes to involvement in research, questions of treatment fidelity, challenges of data collection, amongst others. The decision was made, therefore, to describe the variables rather than attempt to control.

A cluster randomisation design was utilized to avoid the inevitable implementation failures that would occur randomising individual participants to particular treatment streams. Randomisation of individuals would not be possible when, for example, the relevant clinician at that site was unavailable to take another case. Instead it was decided that cases would be allocated by the team. This lack of allocation blinding and randomisation of participants is likely to introduce bias to the allocation of cases. Nevertheless, the cluster randomisation design is likely to detect and account for the variability between groups. The limitations found during this research will have important findings. They will illustrate sources of complexity in seeking to marry evidence and practice in child and mental health services.

The transferability of efficacious treatments into practice is an important issue for clinical researchers and clinicians. It is a complex area of implementation challenges. This article describes the methodological responses to challenges foreseen in conducting a clinical feasibility trial concurrently being conducted within a rural CAMHS. This study protocol illustrates a collaborative clinical research design of potential value to researchers interested in innovative and realistic treatment trials in this area.

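### The protocol says the cluster design will detect and account for an allocation bias that it admits is likely; randomising clinicians and allowing for clustering does neither

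*Protocol article*

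**What the plan says.** The Randomisation section describes "block randomisation of participating clinicians within each of the four sites to either IPT training or TAU". For the next step, from client to clinician, it says "Allocation of clients to clinicians continues as per usual practice of availability".

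The Discussion section explains why clients were not randomised. The practical obstacle it spells out is scarcity: "At any given time a clinician from the allocated treatment stream may not be available at that site to work with the adolescent". It adds that "one site may have only one participating clinician and others only one for each treatment stream". It also mentions concerns of clinicians and researchers about client randomisation, and counts usual-care allocation as an advantage of the design.

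Later in the Discussion the client step is put as "Instead it was decided that cases would be allocated by the team". The consequence is admitted: "This lack of allocation blinding and randomisation of participants is likely to introduce bias to the allocation of cases". The next sentence is the one at issue: "Nevertheless, the cluster randomisation design is likely to detect and account for the variability between groups".

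The Quantitative analysis section makes estimation the main aim, with effect sizes and 95% confidence intervals to be passed to later trials.

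**The concern.** The protocol names a bias and then names the cluster design as what deals with it. These are different problems. Clustering is about precision: clients of one clinician resemble each other, so a naive standard error is too small. Allocation bias is about the estimate itself: if clients who reach IPT clinicians differ in prognosis from those who reach TAU clinicians, the arm contrast measures that difference as well as the treatment.

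Randomising clinicians makes the two sets of clinicians comparable on average. It does not make their clients comparable when clients are assigned afterwards, by people who are not blinded to the arms.

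At stake is what the trial's main quantitative output can be said to show. A planner of the larger trial who relies on the sentence would take the intervals as covering a source of error that they do not cover.

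**Working it through.** **Inputs from the protocol.** Up to 18 clinicians at four sites and a minimum of 60 clients (Sample section). The number 60 was set by feasibility, so there is no power calculation to reproduce. The protocol gives no ICC and no outcome SD.

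**Assumptions.** 9 v 9 clinicians, equal caseloads of m = 60/18 = 3.33, outcome SD 10 T-points, ICC 0.05, and an analysis of clinician means, which is correct for clustering (t with 16 df). Let b be the net difference in prognosis between arms that is due to how cases were assigned.

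**Step 1: what b does to the estimate and to the ICC.** If b is added to every outcome in one arm, the estimated contrast moves by b. Each clinician mean in that arm moves by b, and so does the arm mean, so deviations of clinician means from their arm mean do not change. Nor do deviations of clients from their clinician mean. The within-arm ICC and the standard error are both built from these deviations. They are therefore the same with and without b, and nothing in the clustering analysis registers it.

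**Step 2: what b does to the interval.**

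- Variance of a clinician mean = SD² × [ICC + (1 − ICC)/m] = 100 × [0.05 + 0.95/3.33] = 33.5.
- Standard error of the contrast = √(2 × 33.5/9) = 2.73 T-points.
- Half-width of the 95% interval = 2.12 × 2.73 ≈ 5.8 T-points.
- Coverage = probability that a noncentral t (16 df, noncentrality b/2.73) lies within ±2.12.

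| b (T-points) | noncentrality | coverage of the 95% interval |
|---|---|---|
| 0 | 0 | 95% |
| 2 | 0.73 | 89% |
| 3 | 1.10 | 82% |

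The result depends little on the ICC: for b = 3, coverage is 81% at ICC 0 and 83% at ICC 0.10.

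**Step 3: a check in which the bias arises from client-level choices.** A simulation (4,000 trials per setting, true effect zero, ICC 0.05, correlation 0.5 between the prognosis seen by the team and the outcome) let the team steer by prognosis in a share of cases, standing for those where both arms have an opening. Steering strength is the change in log-odds of arm per SD of prognosis. Site structure was ignored.

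| steering strength | share of cases steered | bias (SD) | coverage | mean estimated ICC | baseline prognosis gap (SD) |
|---|---|---|---|---|---|
| none | – | 0.005 | 94.8% | 0.043 | 0.00 |
| 0.5 | 50% | −0.12 | 93.0% | 0.046 | −0.24 |
| 0.5 | 100% | −0.23 | 89.0% | 0.044 | −0.47 |
| 1 | 25% | −0.10 | 93.7% | 0.045 | −0.21 |
| 1 | 50% | −0.22 | 89.9% | 0.050 | −0.41 |
| 1 | 100% | −0.42 | 74.5% | 0.044 | −0.82 |

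The sign follows from simulating milder cases going to IPT; the opposite steer would reverse it. The estimated ICC lies between 0.043 and 0.050 throughout, so it does not separate steered from unsteered trials. The baseline gap does separate them, but only to the extent that the prognosis the team acts on is recorded.

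**The case against.** The protocol is candid: it states that bias is likely, that key variables cannot be controlled, and that definitive answers need large samples and replication. It presents itself as a feasibility and estimation study. The disputed sentence could also be meant only as a remark that between-clinician variation is allowed for. Baseline values, previous treatment and medication are recorded, so imbalance on measured factors can be seen.

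Much of this stands. The bias is not hidden, and the small study makes no claim to be definitive. But the sentence follows the admission directly and opens by setting itself against it, so it reads as the answer to the bias. Any detection would come from the baseline data, not from randomising clinicians, and would not reach unrecorded factors.

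Three stronger readings are tempting, and the document does not support them.

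- **That the team chooses the arm freely even when both arms have an opening.** This is an inference. How much discretion the team has is not stated.
- **That the Randomisation and Discussion sections give two conflicting rules.** They can be read together: a team can allocate by who is free.
- **That unavailability is the only reason against randomising clients, so nothing stands in the way of a random draw.** The protocol also cites concerns of clinicians and researchers and values usual-care allocation. It offers unavailability as an example: "Randomisation of individuals would not be possible when, for example, the relevant clinician at that site was unavailable to take another case".

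The share of cases with both arms open may also be small, since some sites may have a single participating clinician or one per arm. In the simulation, steering confined to 25% to 50% of cases gave coverage of 89.9% to 93.7%.

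**Conclusion.** The point holds for the assurance. The claim that the cluster design will detect and account for the admitted bias is wrong and should not stand. A systematic difference in clients between arms enters the effect sizes in full, leaves the ICC unchanged, and is not covered by the intervals.

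Its size cannot be known from the document. Under the assumed values, a net difference of 2 to 3 T-points (0.2 to 0.3 SD) lowers coverage to about 89% to 82%, with the estimated ICC staying near 0.05. SD, ICC, the steer, its direction and the share of cases with both arms open are all assumptions or unknowns.

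The point does not show that team allocation was the wrong choice for this service, nor that clients had to be randomised.

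**What to change.** 1. Delete the sentence claiming that the design will detect and account for the variability. State instead that the IPT-TAU contrast is open to selection bias in the assignment of clients, and that the 95% intervals do not cover it.
2. Log for each case which participating clinicians at the site had an opening and how the case was assigned.
3. Compare the arms on baseline RADS-2, CGAS, previous treatment and medication. Adjust the effect estimates for baseline RADS-2 and other recorded prognostic factors, and say that steering on unrecorded factors remains.
4. Show the contrast separately for cases where only one arm had an opening, since the choice of arm was then constrained. With about 60 clients in all, this is a descriptive check only.

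The cost is one log line per case and a little more analysis. Clinician randomisation and usual-care allocation are untouched.

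A central random draw when both arms have an opening is worth considering, here or in the later trial. It would add client-level randomisation to a trial already under way whose authors chose against it, so it is an option and not a required change. The log would show how often such a draw would have been possible.

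### The Discussion credits cluster randomisation with handling an allocation bias that it can neither detect nor remove

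*Protocol article*

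**What the plan says.** The Randomisation section of the protocol article describes "block randomisation of participating clinicians within each of the four sites to either IPT training or TAU". Clients are not randomised: "Allocation of clients to clinicians continues as per usual practice of availability". The Discussion adds: "Instead it was decided that cases would be allocated by the team".

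The Discussion is open about the consequence: "This lack of allocation blinding and randomisation of participants is likely to introduce bias to the allocation of cases". The next sentence is its answer: "Nevertheless, the cluster randomisation design is likely to detect and account for the variability between groups".

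Under Quantitative analysis, the IPT and TAU groups are compared on remission (RADS-2 below the cut-off), clinical improvement, mean depressive symptoms after treatment, and non-completion. Estimation is the main aim, and the effect sizes with 95% confidence intervals are meant to inform later trials.

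**The concern.** The sentence is placed as a reply to the bias just admitted, and it claims a property that the design does not have. Randomisation balances what is randomised, here the clinicians. Clients join afterwards, placed by a team that is not blinded to arm. If more severe or more complex cases tend to go to one arm, that difference enters the IPT-TAU contrast directly. A cluster analysis does not see it as something to correct.

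At stake is the quantity the trial most wants, an effect size for planning. A reader who accepts the sentence would take the interval as covering this source of error. Remission is exposed as well as the mean. The Inclusion/Exclusion criteria admit clients on a diagnosis without requiring a RADS-2 score at the cut-off, so some may start below it, and an uneven share of them would shift an arm's remission proportion.

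**Working it through.** The article gives no figure on this point, so there is none to reproduce. What follows is an illustration.

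**Inputs from the article (Sample section).** At most 18 clinicians at four sites; at least 60 clients; ICC unknown.

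**Assumed inputs, not in the article.** Outcome SD 1; baseline severity imbalance between arms *s* = 0 to 0.5 SD; correlation of baseline severity with outcome *r* = 0.5 to 0.7; ICC 0 to 0.10; 30 clients per arm for the formulas; true treatment effect zero.

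**Step 1: expected difference.** Write the outcome as treatment effect + *r* × severity + clinician effect + residual. Clinicians are randomised, so clinician effects cancel between arms in expectation. The severity term does not:

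bias of the unadjusted post-treatment mean difference = *r* × *s*

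| *s* (SD) | *r* = 0.5 | *r* = 0.7 |
|---|---|---|
| 0 | 0 | 0 |
| 0.3 | 0.15 | 0.21 |
| 0.5 | 0.25 | 0.35 |

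The ICC does not appear in the formula.

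**Step 2: what the ICC does change.** Mean cluster size is 60/18 = 3.33. The design effect is 1 + (3.33 − 1) × ICC, which is 1.00 at ICC 0 and 1.23 at ICC 0.10. The approximate 95% half-width is 1.96 × √((2/30) × design effect), which is 0.51 SD and 0.56 SD respectively. Allowing for clustering widens the interval by about 0.06 SD and leaves it centred on the biased value.

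**Step 3: simulation check.** The settings were 18 clinicians split 9 and 9, 60 clients, cluster means compared with a t interval on 16 degrees of freedom, and 2,500 runs per setting across ICC 0, 0.05 and 0.10.

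| *s* (SD) | Mean bias (SD) | Coverage of the 95% interval |
|---|---|---|
| 0 | about 0 | 95 to 96% |
| 0.3 | 0.14 to 0.22 | 89 to 93% |
| 0.5 | 0.25 to 0.36 | 79 to 88% |

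Small departures from *r* × *s* are simulation error. Raising the ICC from 0 to 0.10 left the bias essentially unchanged.

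**Step 4: detection.** With arm in the model, the between-clinician variance is estimated from clinicians within arms. A shift common to one arm goes into the arm contrast, where outcome data alone cannot separate it from a treatment effect. Even a direct test of baseline severity would be weak: in the same simulation an imbalance of 0.5 SD reached p < 0.05 in 36 to 38% of trials, and one of 0.3 SD in 16 to 18%. That test works only for factors that were measured.

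**Step 5: dependence on the analysis.** The figures in Steps 1 and 3 are for a post-treatment mean with no baseline adjustment. A change score with equal SDs has bias *s*(*r* − 1), of opposite sign: −0.15 to −0.09 SD at *s* = 0.3, and −0.25 to −0.15 SD at *s* = 0.5. Size and direction therefore depend on the analysis, but neither unadjusted version is free of bias when *s* is not zero.

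**The case against.** The strongest defence is that variability between groups means variability between clinicians, for which an ICC-based analysis is suitable. The ICC is indeed a stated purpose of the trial. On that reading the sentence is true, but it no longer answers the bias it is set against, and that bias is left without a reply.

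It is also fair that the article discloses the likely bias, calls the work a feasibility and estimation study, and disclaims definitive answers. No listed analysis step depends on the sentence. This limits the damage, but does not make the claim correct.

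Several stronger readings may tempt a reader, and the article does not support them:

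- **That the two accounts of client allocation contradict each other.** Allocation by availability and allocation by the team are compatible: the team allocates, and availability is the usual basis. The Discussion itself gives clinician unavailability as the reason.
- **That clients enter after their arm is known.** The article does not give the order of eligibility, consent, baseline assessment and assignment. A condensed article may leave that to the full protocol.
- **That the authors decided not to adjust for client mix.** The remark "The decision was made, therefore, to describe the variables rather than attempt to control" follows a list of clinician turnover, attitudes to research, treatment fidelity and data collection. The list is open-ended, but client mix is not named in it.
- **That the lack of a stated covariate adjustment is itself an error.** It may stand in an analysis plan that is not shown.

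**Conclusion.** The point holds for the sentence and for what follows from it. The Discussion admits a likely bias in case allocation and offers as its answer a property that cluster randomisation lacks. The planned IPT-TAU effect sizes, including the post-treatment mean difference and the remission proportion, can be biased in a way their 95% intervals do not reflect.

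On the assumed inputs the bias of an unadjusted post-treatment mean difference runs from 0 to 0.35 SD, against an interval half-width of about 0.51 to 0.56 SD. The lower end is a real possibility, since allocation driven by availability alone could leave the arms similar. The imbalance and correlation values have no source in the article, so the range shows what could happen and does not estimate what has happened. Nor does it follow that a larger trial must inherit the bias: that trial is conditional, and its allocation method is not fixed here. The conclusion that does not depend on these assumptions is that the ICC changes the standard error and not the expected difference.

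**What to change.** 1. Replace the sentence in the Discussion. Suggested sense: *Randomising clinicians does not protect the comparison against bias from the way clients are allocated to them.*
2. Adjust the IPT-TAU comparisons for baseline RADS-2, CGAS, age, sex and baseline medication, with clinician as a cluster effect. If the analysis plan already does this, the Discussion should cite that adjustment, and not the design, as the partial remedy.
3. Report baseline characteristics by arm, and log how each case was allocated.
4. State that adjustment removes only measured imbalance, that unmeasured selection would remain, and that the effect estimates should be used with that caution in planning the larger trial.

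The cost is small. The covariates are already collected, so the burden is some extra analysis, a short allocation record per case, and a less favourable statement of what the design delivers. None of this changes how clients are allocated. A fixed rota is not proposed: the article describes a study already under way with clinicians already randomised, and it gives usual-care allocation as a deliberate advantage of the design.
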